### Patient retention and missing data analysis

Missing data will be presumed to be missing at random (MAR). For our primary analyses, we will use mixed effects model to handle missing data issues based on MAR using Full Information Maximum Likelihood (FIML) estimation.

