## Materials and methods

### Study design, eligibility, and recruitment

This is a multi-institutional prospective, observational cohort study of patients electing to undergo either ESS or continued medical therapy (CMT) for CF-related CRS after having failed initial medical therapy. Patients will be enrolled at one of nine participating CF centers across the US.

Potential participants will be considered for study inclusion if they are adults (age 18–99 years), diagnosed with CF by genetic testing and/or sweat chloride testing, and have persistent CRS based on multi-disciplinary guidelines [5, 6]. Patients who underwent ESS in the 12 months preceding study enrollment, plan to have follow-up care at a non-participating institution, are unable to complete post-operative outcome measures, or started or modified new CFTR modulator therapy within 90 days of study enrollment will be excluded **(Table 1).** Participants consenting to study will be included in one of two study groups: those who elect to undergo ESS and those who pursue CMT. Extent of surgery, including use of extended approaches, will be tracked and analyzed.

**Table 1 pone.0310986.t001:** Inclusion and exclusion criteria.

Inclusion Criteria	Exclusion Criteria
Age 18 years or older	Underwent ESS in past 12 months
Diagnosed with CF as established by genetic testing combined with clinical assessment and/or sweat chloride	Will obtain follow up care at nonparticipating institutions
Diagnosed with CRS by multidisciplinary sinusitis guidelines	Unable to complete outcome measures
CRS symptoms persisting beyond initial medical treatment	Started new CFTR modulator therapy less than 90 days prior to screening or anticipated to begin during study period

ESS, endoscopic sinus surgery; CF, cystic fibrosis; CRS, chronic rhinosinusitis, CFTR, cystic fibrosis transmembrane receptor

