### Statistical methods

For all objectives, we will verify predictive model assumptions and test goodness-of-fit, considering alternative models if needed. We will account for potential site-specific differences as fixed effects in our models. Other methods to address site clustering include mixed effects models and generalized estimating equations.

For Objective 1, mixed effects model will be used to assess the impact of ESS versus CMT on ppFEV_1_ changes at initial and subsequent visits. Fixed effects will include baseline FEV1 (FEV1 > 80% predicted, <80% and > 50%, and <50%), CF variant status, use of CFTR modulator therapy, sex, prior sinus surgery, time and treatment; patients will be treated as random effects. An unstructured variance approach will model within-subject errors, and we will explore other covariance if needed. As exploratory analysis, we will compare ppFEV_1_ from a year before enrollment to post-treatment values using the same model. Using a generalized linear model with a Poisson distribution and prior year data, we will assess the impact of ESS versus CMT on exacerbation rates and antibiotic use, complemented by descriptive statistics for sociodemographic factors.

For Objective 2, we will describe patient characteristics using summary statistics. Treatment effects on patient reported-outcome measures (CFQ-R, SNOT-22, PHQ-9, PSQI, CFQ, QOD, and SIT) will be explored via a mixed effects model, adjusting for multiple comparisons using a gate-keeping procedure and assessing for self-report bias in patient-reported outcomes by comparing them to FEV1.

For Objective 3, we will correlate productivity costs with patient demographics, disease factors, pulmonary status, and QOL impairment. We will use a mixed effects model to evaluate these outcomes.

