### Statistical power and sample size

Sample size and power were calculated using software G Power (v. 3.1). Type I error will be controlled at two-sided 5% level. Sample size calculations were initially based on our primary QOL outcome measure (SNOT-22 scores) for objective 2, given strong evidence of improvements in the literature [33]. This was then applied to objective 1. For objective 2, detecting SNOT-22 score changes pre- and post-12 months ESS requires 9 patients for 80% power. To determine changes between treatment groups over time, considering a potential 30% cross-over between ESS and CMT groups, 106 patients are needed for 80% power, as indicated by prior data [34]. Accounting for 20% potential dropouts, our recruitment target is 150 participants, with an anticipated enrollment of approximately 170 across all centers.

Regarding ESS effects on ppFEV_1_, previous mixed results complicate clear expectations to use in power calculations for objective 1. Assuming 170 participants (factoring in 20% dropout), we will have 80% power to detect a 1.6% ppFEV_1_ change for objective 1 and a 2.3% ppFEV_1_ change for objective 1 accounting for HEMT.

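### Full maximum likelihood for the primary mixed models makes the standard error of the between-patient ESS v CMT effect about 5-8% too small, a modest bias that REML removes under the same MAR assumption

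*Protocol article*

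**What the plan says.** The protocol article fixes the estimator under Patient retention and missing data analysis: for the primary analyses, "we will use mixed effects model to handle missing data issues based on MAR using Full Information Maximum Likelihood (FIML) estimation". REML and small-sample degrees of freedom are not mentioned anywhere in the article.

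Statistical methods describes the Objective 1 model. Its fixed effects are baseline FEV1 in three bands, then "CF variant status, use of CFTR modulator therapy, sex, prior sinus surgery, time and treatment; patients will be treated as random effects". On the covariance it says: "An unstructured variance approach will model within-subject errors". For all objectives it adds: "We will account for potential site-specific differences as fixed effects in our models". It also mentions mixed models and generalized estimating equations as other ways to handle site clustering. The study design section gives the number of sites: "Patients will be enrolled at one of nine participating CF centers across the US".

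Statistical power and sample size states: "Type I error will be controlled at two-sided 5% level".

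**The concern.** Maximum likelihood treats the fixed effects as known when it estimates variances, so it divides by the number of patients and not by the residual degrees of freedom. The loss is negligible when few parameters are fitted at patient level. Here there are many relative to the sample, chiefly because of the site terms. Treatment group is itself a patient-level factor, and the listed model has time and treatment but no treatment-by-time term. Read as written, the treatment coefficient is the kind of effect whose standard error ML understates.

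The error always goes the same way: intervals too narrow, and a difference between ESS and CMT declared somewhat more often than the stated 5%. The reason given for FIML, validity under MAR, does not require it.

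**Working it through.** **Inputs**
- Patient-level parameters, from Statistical methods: intercept 1, baseline FEV1 bands 2, variant status 2 (three levels assumed; the article does not give the number), modulator use 1, sex 1, prior surgery 1, treatment 1. Sum: 9.
- Nine sites as fixed effects: 8 more, so p = 17.
- Sample sizes, from Statistical power and sample size: 106 needed, 150 targeted, 170 anticipated, 20% dropout (150 × 0.8 = 120). From Current status: 87 enrolled by October 2023.
- Stated level: two-sided 5%.

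**Closed form for a between-patient effect**

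ML standard error ÷ unbiased standard error = √((n − p)/n).

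Actual type I error with a z test = P(|t| > 1.96 × √((n − p)/n)), with t on n − p degrees of freedom.

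Example, n = 150 and p = 17: √(133/150) = 0.942; 1.96 × 0.942 = 1.846; P(|t| > 1.846) on 133 degrees of freedom = 6.7%.

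| n | SE ratio, p = 17 | Type I error, p = 17 | SE ratio, p = 9 (no site terms) | Type I error, p = 9 |
|---|---|---|---|---|
| 170 | 0.949 | 6.5% | 0.973 | 5.8% |
| 150 | 0.942 | 6.7% | 0.970 | 5.9% |
| 120 | 0.926 | 7.2% | 0.962 | 6.2% |
| 106 | 0.916 | 7.6% | 0.957 | 6.4% |
| 87 | 0.897 | 8.3% | 0.947 | 6.7% |

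The stated 5% is not reproduced in any row. These ratios do not depend on the outcome SD or on the within-patient correlation. Little of the excess comes from using z in place of t: with an unbiased standard error and p = 17, a z test gives 5.2% at n = 150 and 5.3% at n = 106.

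**Simulation under no effect**

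Settings: unstructured covariance, nine sites, 17 patient-level terms, monotone MAR dropout of about 16-21%, assumed SD 6 and correlation 0.6, equal groups, 3,000 runs per setting (Monte Carlo error about 0.4 points). Each range covers two versions, with and without baseline as part of the outcome vector. REML was tested against t on n − p degrees of freedom for the two between-patient contrasts.

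| Contrast | n | SE, ML ÷ REML | Type I error, ML with z | Type I error, REML with t |
|---|---|---|---|---|
| Average over visits | 150 | 0.942 | 6.7-7.7% | 5.0-5.7% |
| Average over visits | 106 | 0.917-0.918 | 6.7-8.7% | 4.8-5.6% |
| Average over visits | 87 | 0.899-0.900 | 8.9-9.0% | 5.5% |
| Month 12 | 150 | 0.958-0.959 | 6.1-6.3% | 4.6-5.4% |
| Month 12 | 106 | 0.939-0.942 | 6.3-7.9% | 4.5-5.6% |
| Month 12 | 87 | 0.925-0.928 | 7.1-7.8% | 5.2-5.4% |
| Treatment by time | 150 | 0.992 | 5.1-5.5% | 4.7-5.1% |
| Treatment by time | 106 | 0.988-0.989 | 5.4-5.8% | 4.8-5.2% |
| Treatment by time | 87 | 0.986 | 5.8-5.9% | 5.1-5.2% |

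The simulated standard-error ratios for the visit average match the closed form. REML returns both between-patient contrasts to 5% within about two Monte Carlo errors, under the same dropout.

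**The case against.** The strongest objection concerns the contrast. The objectives speak of change in outcomes, the profile analysis tests whether trajectories are parallel, and the sample size refers to change between groups over time. If inference rests on a treatment-by-time contrast, with covariates that do not interact with time, ML costs about 1% in the standard error and there is practically no defect. This stands as a limit. A reader might infer that every ESS v CMT interval in the primary analysis is too narrow, and the documents do not support that. Nor do they settle the matter the other way: the listed model contains treatment but no interaction, and a month-12 difference remains affected.

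Second, 17 is not a firm count. Eight of the terms are sites, for which the article allows other approaches, and the levels of variant status are assumed. Without the site terms the excess is smaller but has the same sign. Objectives 2 and 3 list no covariates of their own, so these figures do not carry over to them.

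Third, under MAR likelihood the observed visits of dropouts stay in, so counting completers only (120) overstates the problem for 150 recruits. That is right, and 150 and 170 are therefore shown as well.

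A reader might also infer much larger inflation in the surgically naive subgroup or after early closure. The article gives no subgroup size and describes that analysis as exploratory. The figure of 87 is a progress count with enrolment continuing.

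Finally, degrees of freedom are commonly left to the analysis plan, and some authors use FIML loosely for any likelihood analysis under MAR. The article nevertheless names full maximum likelihood, and the point is about that stated choice.

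**Conclusion.** The point holds as a modest one. With the listed covariates and nine sites as fixed effects, the stated estimator makes the standard error of the between-patient treatment effect about 5-8% too small at n = 106 to 170, and a z test then runs at about 6.5-7.6% against the stated 5%. At n = 87 it is about 8%, and a little higher in simulation. If site is not a fixed effect, it is about 5.8-6.4% at n = 106 to 170. A month-12 difference runs at about 6-8% in simulation at n = 87 to 150, and a pure treatment-by-time contrast at about 5-6%.

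The result assumes three variant-status levels, a z reference distribution (the article names none) and, for the simulation only, the SD, correlation and equal groups given above. It should not be read as showing that REML holds 5% at any sample size: this was checked at 87 to 150 patients with n − p degrees of freedom, and Kenward-Roger itself was not run.

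**What to change.** In the missing-data section, replace the FIML wording with a statement such as: mixed models will be fitted by REML with small-sample degrees of freedom (for example Kenward-Roger), using all observed visits under the MAR assumption; ML will be used only for likelihood-ratio comparison of mean structures. Apply it to the mixed models of all three objectives and to the subgroup models, so that one method runs throughout.

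The cost is one sentence and a software option. Intervals for between-patient effects become slightly wider, with a correspondingly small loss of nominal power. No change to data collection or to the missing-data assumption is needed.

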### Data management

Study data will be managed using REDCap, a secure application offering user-friendly forms, real-time data entry validation, and de-identified data export features. The database is hosted at UCLA Health for centralized data handling with secure, electronic access provided to all external study teams.

### Patient and public involvement

This study engaged PwCF+CRS from the initial design stage. Through focus group interviews, we gleaned PwCF’s preferences regarding post-ESS outcomes, ensuring that our research aims aligned with their priorities. This feedback directly shaped our research questions and outcome measures of pulmonary function, olfaction, frequency of PEx, and QOL. When PwCF+CRS were queried about potential study design options, individuals were much more likely to participate in an observational study than a trial randomized to ESS or CMT, leading to the selection of an observational study design. We aim to publish study results with CF Foundation’s community members, healthcare professionals, and CF researchers.

### Ethics and dissemination

This study was registered on ClinicalTrials.gov (NCT04469439) and conducted in compliance with the Declaration of Helsinki and International Conference on Harmonization and Good Clinical Practice guidelines and applicable regulatory requirements. Each participating site received approval from their local Institutional Review Board (IRB). IRB approval for the primary coordinating site was granted by UCLA approval number 20–002079.

The results of this study will be disseminated during national and international scientific conferences and published in peer-reviewed journals. Stakeholders will be informed via CF Foundation’s research newsletters.

## Current status

This study started in August 2019 and as of October 2023, we have 87 enrolled participants. We are continuing to enroll at all sites.

## Discussion

In this multi-institutional prospective study, our primary objective is to evaluate post-ESS outcomes in PwCF+CRS in the era of highly effective modulator therapy. We will examine pulmonary function, PEx rates, antibiotic use, QOL, productivity loss, and health utility value over a 12-month period post-ESS. Our study uniquely will compare the impact of HEMT on outcomes between PwCF+CRS who undergo ESS and those opting for CMT.

Our study leverages a prospective, multi-institutional design, mitigating the limitations of small sample size and common biases associated with retrospective review. We acknowledge the limitations of an observational design instead of a randomized controlled clinical trial (RCT). This design was selected based on challenges of randomizing surgical interventions and PwCF’s reservations about randomization to ESS or delayed intervention [35]. Many PwCF expressed reluctance to be randomized, which would likely have led to enrollment difficulties in a RCT [35]. Further, there are notable difficulties in randomizing study participants to surgical interventions that require general anesthesia. These include the high cost of interventions that the study may have to fund (ESS estimated at > $10,000 USD/case) [36] and ethical considerations, such as employment of sham surgery in a placebo control arm [37]. To minimize potential bias, we will employ advanced statistical techniques like MPA and propensity score matching. Our method is poised to produce robust data, including endpoints that can provide some of the first insights of CRS outcomes in the current era. Data accumulated from this study will provide preliminary data upon which to design future trials.

In contrast to prior post-ESS studies evaluating ppFEV_1_ and demonstrating mixed results [12, 13], our research will thoroughly examine the relationship between ESS and pulmonary function in PwCF by assessing not only spirometry, but also PEx and antibiotic use, all crucial outcomes due to their significant impact on morbidity, QOL, and associated costs [36]. Previous findings from the period before widely available HEMT indicate that people without CF who undergo ESS have improved sinonasal symptoms and CRS-specific QOL [7, 37]. However, this study will comprehensively evaluate in the HEMT era the impact of ESS on multiple validated metrics such as CF-specific QOL, CRS-specific QOL, sleep, depression, olfaction, and cognition. Similar to non-CF individuals with CRS, PwCF suffer from depression [38], poor sleep [39], headaches [40], impaired olfaction [41], and cognitive limitations [42]. Prior work has demonstrated improvement in these comorbid conditions after ESS in non-CF+CRS individuals [43–46]; however, depression, sleep, and olfactory outcomes post-ESS require further study in PwCF who have systemic disease and a vastly different burden than people with CRS without CF.

Annual productivity loss per person with CF is estimated at $15,935 [47], compared to non-CF, refractory CRS patients with PL of $10,077 [48, 49]. CRS patients have demonstrated diminished work performance or disease-related absenteeism that may be magnified in PwCF who may require daily routine treatments [48], for those not on HEMT, or who require additional care related to PEx [50]. Prior research has shown that ESS is associated with improvements in PL in non-CF+CRS patients [51], and this is an area meriting investigation in PwCF+CRS. HUV is a measure of generalized QOL that has been used for the valuation and comparison of treatment in CRS and CF [52, 53]. The study of HUV in CF has primarily focused on lung transplantations and management of PEx [52]. With the exception of PwCF with no exacerbations, CF patients have lower mean HUV compared to the general US population (0.85 [SD 0.81]) and non-CF CRS population (0.81[SD 0.13]) [53]. In non-CF+CRS patients, prior research has indicated clinically relevant improvements in HUV post-ESS, unlike those on CMT [54]. Other prior work has shown that HEMT leads to clinically relevant improvements in HUV [55, 56]. Our study seeks to explore ESS’s impact on HUV for PwCF+CRS and will assess if HUV improvement occurs on top of that previously removed with HEMT.

Our proposed study extends beyond pulmonary function to encompass QOL, PL, and HUV outcomes, reflecting the evolving landscape of cystic fibrosis management as lifespans continue to lengthen with expanding use of HEMT [57]. By exploring the interplay between post-ESS outcomes and HEMT, we aim to better understand treatment outcomes and optimize management of CF-related CRS. We also plan to characterize olfactory dysfunction’s impact on eating patterns and nutritional status, which hold significant implications for pulmonary function in PwCF [58]. The results from this study will serve as valuable preliminary insights for designing future trials and refining treatment strategies.

In conclusion, investigating pulmonary function, QOL, and health economic outcomes related to CF-CRS presents a significant opportunity to expand understanding of this disease complication. The proposed study will bring together participants across multiple CF centers to garner a large sample size. We anticipate uncovering valuable insights into the optimal management of CF-CRS. Several questions remain unanswered, such as the long-term effects of ESS and HEMT, particularly in relation to depression, sleep, and olfactory outcomes in PwCF. Future research should delve further into these areas, providing a more nuanced understanding of the multifaceted impact of ESS in PwCF+CRS.
